# A randomised controlled trial to determine the clinical and cost effectiveness of thulium laser transurethral vaporesection of the prostate (ThuVARP) versus transurethral resection of the prostate (TURP) in the National Health Service (NHS) – the UNBLOCS trial: a study protocol for a randomised controlled trial

**DOI:** 10.1186/s13063-017-1916-5

**Published:** 2017-04-17

**Keywords:** UNBLOCS, Prostate, Surgery, Lower urinary tract symptoms, Benign prostatic obstruction, Randomised controlled trial, Transurethral resection of the prostate, TURP, Thulium laser transurethral vaporesection of the prostate, ThuVARP

## Abstract

**Background:**

Transurethral resection of the prostate (TURP) has been the standard operation for benign prostatic obstruction (BPO) for 40 years, with approximately 25,000 procedures performed annually, and has remained largely unchanged. It is generally a successful operation, but has well-documented risks for the patient. Thulium laser transurethral vaporesection of the prostate (ThuVARP) vaporises and resects the prostate using a surgical technique similar to TURP. The small amount of study data currently available suggests that ThuVARP may have certain advantages over TURP, including reduced blood loss and shorter hospital stay, earlier return to normal activities, and shorter duration of catheterisation.

**Design:**

A multicentre, pragmatic, randomised, controlled, parallel-group trial of ThuVARP versus standard TURP in men with BPO. Four hundred and ten men suitable for prostate surgery were randomised to receive either ThuVARP or TURP at four university teaching hospitals, and three district general hospitals. The key aim of the trial is to determine whether ThuVARP is equivalent to TURP judged on both the patient-reported International Prostate Symptom Score (IPSS) and the maximum urine flow rate (Qmax) at 12 months post-surgery.

**Discussion:**

The general population has an increased life expectancy. As men get older their prostates enlarge, potentially causing BPO, which often requires surgery. Therefore, as the population ages, more prostate operations are needed to relieve obstruction. There is hence sustained interest in the condition and increasing need to find safer techniques than TURP. Various laser techniques have become available but none are widely used in the NHS because of lengthy training required for surgeons or inferior performance on clinical outcomes. Promising initial evidence from one RCT shows that ThuVARP has equivalent clinical effectiveness when compared to TURP, as well as other potential advantages. As ThuVARP uses a technique similar to that used in TURP, the learning curve is short, potentially making it also very quickly generalisable. This randomised study is designed to provide the high-quality evidence, in an NHS setting, with a range of patient-reported, clinical and cost-effectiveness outcomes, which will underpin and inform future NICE guidance.

**Trial registration:**

ISRCTN registry, ISRCTN00788389. Registered on 20 September 2013.

**Electronic supplementary material:**

The online version of this article (doi:10.1186/s13063-017-1916-5) contains supplementary material, which is available to authorized users.

## Background

The prostate gland sits at the exit of the bladder like a collar, and as men get older their prostates enlarge. This can commonly result in either urinary retention, an inability to completely empty the bladder, or in bothersome lower urinary tract symptoms (LUTS) secondary to benign prostatic obstruction (BPO), such as slow and intermittent urinary stream. These conditions severely affect a man’s quality of life resulting in worsening physical and social functioning, vitality, and mental health [1]. Bothersome LUTS secondary to BPO with an International Prostate Symptom Score (IPSS) of at least 11 and a maximum urine flow rate (Qmax) less than 15 ml/s affects 2.5 million men aged 40–79 in the UK, with 44,000 new cases diagnosed annually [2]. LUTS may be treated by watchful waiting or drugs, but many will require prostate surgery, including almost all men who present in urinary retention.

Around 25,000 prostate operations are performed annually in the UK for men with BPO to relieve obstruction. Transurethral resection of the prostate (TURP), the gold standard operation, accounts for around 80% of these operations. TURP has been used widely for the last 40 years, and although it is generally a successful procedure, it is associated with small but significant risks. It has a 30-day mortality of 0.3%, and a range of morbidities including transurethral resection (TUR) syndrome (1%), which is due to the absorption of irrigating fluid leading to confusion and collapse; haemorrhage during the operation (transfusion rate: 5%); and subsequent urinary tract infections (up to 20%) [3]. These morbidities result in delayed discharge and increased re-admissions, increased primary care resource utilisation, considerable distress to patients and additional costs to the National Health Service (NHS).

The well-known risks for both mortality and morbidity from TURP have meant that many alternatives have been assessed. Various laser alternatives have been marketed, but none have become widely used. This is due, in part, to a long learning curve, or inferior performance regarding clinical outcomes, reducing the wider uptake. In fact, Hospital Episode Statistics (HES) data shows that the percentage of laser procedures has only increased in England by 2% over the past 5 years, from 2894 in 2009/10 to 2958 in 2011/12. This is despite the accepted advantages of laser prostatectomy, including lower risk of peri-operative complications, shorter catheterisation time and reduced hospital stay [4]. Recent National Institute for Health and Care Excellence (NICE) clinical guidelines CG97 recommend offering TURP or holmium laser enucleation (HoLEP) for BPO surgery [5]. Although HoLEP is a long-established effective procedure, it is only used in a few centres, due to a very long learning curve reducing its generalisability, and indeed NICE recommends that this procedure is only performed in centres specialising in the technique.

This study, UriNary oBstruction relieved by Laser Or Conventional Surgery (UNBLOCS), is evaluating a new laser technique called thulium laser transurethral vaporesection of the prostate (ThuVARP). A thulium laser technique has been chosen which vaporises and resects the prostate because it uses a surgical technique similar to TURP, and will therefore enable a short learning curve making it quickly generalisable. It was first made available in 2004 in the UK but has only been compared in one randomised controlled trial (RCT) in China against TURP [6]. Based on this RCT and one non-randomised prospective controlled trial with small and medium-sized prostates [7], the European Association of Urology (EAU) guidelines have stated that ThuVARP showed equivalent efficacy in comparison with TURP [8]. However the thulium patients had shorter catheterisation and hospitalisation times, with adverse events being lower than for TURP (intra-operative and post-operative bleeding; level of evidence 1b).

NICE in its 2010 Male LUTS Guidelines [5] stated that the evidence base is inadequate to give clear guidance in terms of clinical and cost effectiveness of laser vaporesection techniques. NICE identified that research in this area, in the form of a randomised controlled trial, would help inform future guidance on the use of laser vaporesection techniques for men with LUTS or urinary retention, who need surgery.

### Rationale for the trial

The general population has an increased life expectancy, resulting in an ageing population. As BPO is a disease of older men, the number of patients with the condition is expected to grow by almost 50% by the year 2025, increasing the need for BPO surgery [2]. Furthermore, as the operation is increasingly conducted on older men (42% of the TURP operations in 2014–2015 were on patients older than 75 years), the risks of surgery associated with TURP will continue to increase. There is therefore sustained interest in the condition and increasing need to find safer techniques than TURP. The potential advantages of reduced blood loss, shorter hospital stay and earlier return to normal activities make laser vaporesection techniques attractive to both patients and health care providers. ThuVARP would allow urologists to operate on a wider range of men, including potentially those who are more frail and older, but with less risk. However, there is uncertainty about the degree of symptom improvement and improvement in quality of life in the short and longer term, which this trial addresses. Now is the ideal time to conduct the trial as the procedure has not yet been widely taken up across the UK.

An additional reason for early evaluation of ThuVARP is the promise it offers to convert BPO surgery from an inpatient operation into a day-case procedure. Shortened stay is increasingly important for the NHS both because of the increasing cost of inpatient beds, shortage of inpatient beds due to an ageing and increasingly co-morbid population, and the risk longer hospital stays present for such patients, for example of hospital-acquired infections.

In summary, although there is little existing work on ThuVARP, promising initial evidence from one RCT suggests that ThuVARP has equivalent clinical effectiveness when compared to TURP, albeit in a single Chinese centre. Our randomised study is designed to provide the high-quality evidence, in an NHS setting with a range of patient-reported, clinical and cost-effectiveness outcomes, which will underpin and inform future NICE guidance.

## Methods/trial design

### Study aims and objectives

The key aim of this research is to determine whether ThuVARP is equivalent to TURP in men with BPO treated within the NHS, judged on a patient-reported symptom severity score (IPSS) and the maximum urine flow rate (Qmax).

We will answer the following primary question: what is the relative clinical effectiveness of ThuVARP and TURP in improving patient-reported LUTS as measured by the International Prostate Symptom Score (IPSS) patient-reported questionnaire, and the objective measure of maximum urine flow rate (Qmax), 12 months after surgery?

Secondary research questions are:How do the two procedures compare in terms of peri-operative outcomes?What is the cost-effectiveness of ThuVARP as compared to TURP in terms of the two primary outcomes and quality-adjusted life years (QALYs: the primary economic outcome)?What is the comparative impact of each treatment on patient-reported LUTS, erectile function, quality of life and general health?What is the comparative satisfaction of men with each type of surgery?What is the comparative effectiveness of these operations in men who present with LUTS as opposed to urinary retention?What are men’s experiences of both procedures, including those presenting with LUTS or urinary retention?

### Trial design

This is a multicentre, pragmatic, randomised, controlled, parallel-group trial of thulium laser transurethral vaporesection of the prostate (ThuVARP) versus standard transurethral resection of the prostate (TURP) in men with benign prostatic obstruction (BPO). Randomisation is at the patient level so men were randomised 1:1 to receive either ThuVARP or TURP.

This study is powered to establish equivalence in clinical improvement. We are specifying differences in Qmax and IPSS of no greater than 4 ml/s and 2.5 units respectively, as demonstrating equivalence.

Follow-up is at 6 weeks, 3 and 12 months after surgery for the patient-reported outcome (PRO) IPSS, and at 3 and 12 months for the maximum urine flow rate (Qmax), with 12 months being the primary endpoint. Patients are asked to complete other patient-reported outcomes at 6 weeks after surgery (by post), and after 3 and 12 months. The study flow diagram is provided in Fig. 1 and the Standard Protocol Items: Recommendations for Interventional Trials (SPIRIT) checklist in Additional file 1.

**Fig. 1 Fig1:**
[figure not shown]
Study flow diagram. *BPO* benign prostatic obstruction, *CRF* case report form, *PVR* post-void residual, *ThuVARP* thulium laser transurethral vaporesection of the prostate, *TURP* transurethral resection of the prostate

### Setting

Participants have been recruited and operated on at seven UK centres: four university teaching hospitals and three district general hospitals. Each of the centres in the trial performs between 150 and 400 benign prostate operations per year.

### Study duration

Recruitment for the trial began in June 2014 and completed at the end of December 2016. Twelve-month follow-up for all participants will complete by the end of November 2017.

### Participants

As this is a pragmatic trial, it includes men who are suitable for TURP referred to secondary care for assessment with a view to requiring BPO surgery, presenting with either bothersome LUTS or urinary retention secondary to BPO.

#### Inclusion criteria

Men who were suitable for TURP, either in urinary retention or with bothersome LUTS, secondary to BPO.

#### Exclusion criteria

Patients with:Neurogenic LUTSProstate cancerPrevious prostate or urethral surgeryA prostate-specific antigen (PSA) outside of the normal age-related range and who had not had prostate cancer excludedMen who were unable to give informed consent or complete trial documentation

### Interventions

Patients were randomised 1:1 to receive either the TURP or ThuVARP procedure. As this is a pragmatic study, centres continued to use their usual practices, for example, with respect to whether or not they did pressure-flow urodynamics as part of patient selection, or how they undertook the TURP procedure, e.g. use of monopolar or bipolar TURP. All trial surgeons underwent training on the ThuVARP technique as described below.

Patients undergoing concomitant procedures during their BPO surgery were included in the trial, and details of their additional surgery recorded.

All adverse events are recorded and serious adverse events notified to the appropriate authorities (Research Ethics Committee and Sponsor) within specified timelines.

### Surgeon training on the laser

ThuVARP uses laser technology to vaporise and resect the prostate while TURP uses electric current to resect the prostate. ThuVARP essentially uses the same surgical skill-set as for the TURP procedure which is part of core practice for all urologists, including trial surgeons who performed both procedures. The experience of the Chief Investigator and other urologists, in the UK and Europe, indicate that a maximum of 15 ThuVARP laser cases can assure competence in the ThuVARP laser procedure.

All surgeons were mentored by the Chief Investigator (CI) or another Principal Investigator (PI) already certified as competent with the ThuVARP technique, and certified by an independent assessor, using standard criteria, before the official study commenced. First, surgeons observed the CI/PI performing one to two cases. The CI/PI then observed the surgeons in each centre perform two to five cases during site visits. The surgeons then performed five to ten cases without supervision, following their respective Trust’s clinical governance and audit guidelines. Competency was assessed with the Intercollegiate Surgical Curriculum Programme work-based assessment (ISCP-WBA) by an independent assessor. If competency was not achieved at this stage, then further cases would have been observed and training provided by the CI until the competency criteria were met, however in practice all surgeons were signed off as competent at their first assessment.

### Withdrawal

Participants remain in the trial unless they choose to withdraw or if they are unable to continue for a clinical reason. If a participant withdraws consent, participant questionnaires are not collected. However, permission is sought for the research team to continue to collect outcome data from their health care records. Participants are informed in the Patient Information Sheet (PIS) that they have the right to withdraw all personal data held by the study, but otherwise this data is retained.

### Outcome measures

Two key co-primary outcomes were selected, measured at 12 months, based on a well-established and validated patient-reported outcome (PRO), the International Prostate Symptom Score (IPSS) [9], and the urodynamic clinical measure of maximum urine flow rate (Qmax: ml/s) which is used in all BPO trials. These outcomes address the primary research question for the trial.

The IPSS and Qmax are internationally accepted, and the most frequently used primary outcomes in BPO studies, thereby making results from this study comparable to others. There are no core outcomes measures for BPO listed in the COMET Initiative website.

Key secondary outcome measures include other well-validated PROs and answer the trial research questions:Clavien-Dindo classification of surgical complications [10]Length of hospital stay and transfusion ratesInternational Consultation on Incontinence Questionnaire – Male Lower Urinary Tract Symptoms (ICIQ-MLUTS) (for symptom bother)International Index of Erectile Function (IIEF) and ICIQ-MLUTSsex (measures of erectile function)ICIQ-LUTSqol (condition-specific quality of life score)EuroQol Group’s five-dimension health status questionnaire (EQ-5D-5L) (preference-based general quality of life measure)ICIQ-satisfaction (measures satisfaction with surgery outcomes) to assess the full impact of the intervention on patients and the NHSResource use for the year following randomisation to inform the cost-effectiveness analysisInterviews following surgery, for qualitative analysis of men’s experiences of both procedures

In addition to these key secondary outcomes, other secondary outcomes are:Post-operative catheterisation timeHaemoglobin (blood loss during surgery)Serum sodium (absorption of irrigation fluid)Post-void residual urine

### Assessment and follow-up

The timing of our outcome measurements are summarised in Fig. 2 (schedule of enrolment, interventions, and assessments) and described below.

**Fig. 2 Fig2:**
[figure not shown]
Schedule of enrolements, interventions and assessments

#### Clinical outcomes

Urine flow rate (Qmax), post-void residual (PVR) and voided volume (VV) were measured before surgery in men who were able to void without a catheter. The most recent existing measures were used if they were performed within 90 days of informed consent. PVR and VV were measured post-operatively, and Qmax, PVR and VV at 3 and 12 months post-surgery. These follow-up flow measures are not collected if men are catheterised, but trial without catheter (TWOC) data is recorded.

Blood parameters were also measured at baseline and post-operatively, including full blood count (FBC) and urea and electrolytes (U&Es).

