#### Patient reported outcomes

Participants receive the UNBLOCS Symptoms/Surgery Questionnaire at baseline in clinic, 6 weeks post-surgery (by post), and at 3 and 12 months post-surgery in clinic (with the option to take home and return in pre-paid envelope if preferred). The questionnaire contains questions from standardised outcome instruments for urinary and sexual symptoms (listed in Fig. 2) and the baseline questionnaire had versions for men who were using a catheter and those who were not, as some items were not relevant for catheterised patients. Participants who are catheterised at the time of the 3- or 12-month questionnaires are instructed to only answer the questions that they feel able to. The Bladder Diary was given to participants at their baseline clinic and at their 3 and 12 months clinics if they do not require a catheter to void at the time. The Bladder Diary is used to record fluid intake, frequency and volume of micturition and bladder sensation and use of pads over 3 days, and is returned in a pre-paid envelope.

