### Statistical analysis

All data analysis will be in accordance with the Consolidated Standards of Reporting Trials (CONSORT) guidelines extension for non-inferiority and equivalence trials [15]. A full statistical analysis plan will be developed and agreed by the Data Monitoring Committee and the Trial Steering Group prior to undertaking any analyses of the trial data.

Descriptive statistics will be used to compare patient baseline characteristics between the two treatment groups. The primary comparative analyses will be conducted on an ‘as allocated’ basis and will employ multivariable linear regression to investigate equivalence in Qmax and IPSS between ThuVARP and TURP at 12 months. Analyses will adjust for stratification variables (centre and retention). Interpretation of results will focus on observed differences, and 95% confidence intervals for the between-group comparisons, to determine whether clinically important differences between ThuVARP and TURP are unlikely. Missing data will be imputed using multiple imputation modelling. Additional sensitivity analysis will explore the impact of missing data by using complete cases only. Sensitivity analyses will also consider adjustment for baseline measures of Qmax and IPSS (with clinically sensible values imputed for those with retention, for example a Qmax of zero) any variables demonstrating imbalance at baseline. Consideration will also be given to surgeon effects using mixed-effects models.

As randomisation will occur close to the time of surgery, a significant cross-over between treatment groups is thought unlikely, but any departures from protocol are likely to make the treatment groups more similar. In a superiority trial an ‘as allocated’ (or intention-to-treat) analysis is a conservative approach. In an equivalence trial, such as this, where the objective is to demonstrate that treatments have a similar effect, a per protocol analysis may be a more conservative approach, but prone to bias. An alternative is randomisation-based efficacy estimators (complier average causal effect models (CACE)) which maintain randomisation [16]. If protocol deviations occur we will conduct sensitivity analyses to assist with the interpretation of the primary result, these will include CACE and per protocol analyses with discussion of any likely bias in the resulting estimates.

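### No stated analysis of 12-month Qmax counts a man known to be catheterised as a failure; his value is imputed from voiders or dropped, which can distort the comparison if catheter dependence differs between arms

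*Protocol article*

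**What the plan says.** **Collection.** Under Clinical outcomes, flow is measured at 3 and 12 months, with one exception: "These follow-up flow measures are not collected if men are catheterised, but trial without catheter (TWOC) data is recorded". Under Patient reported outcomes, men with a catheter at the 3- or 12-month questionnaire "are instructed to only answer the questions that they feel able to", so their IPSS may be partial.

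**Analysis.** Under Statistical analysis, the primary comparison "will employ multivariable linear regression to investigate equivalence in Qmax and IPSS between ThuVARP and TURP at 12 months". The rule for gaps is a single sentence: "Missing data will be imputed using multiple imputation modelling". The check on that rule is: "Additional sensitivity analysis will explore the impact of missing data by using complete cases only".

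**Retention.** The only value proposed for a man who cannot void belongs to a different analysis, a sensitivity analysis with "adjustment for baseline measures of Qmax and IPSS (with clinically sensible values imputed for those with retention, for example a Qmax of zero". It concerns the baseline covariate and not the 12-month outcome.

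**What is deferred.** "A full statistical analysis plan will be developed and agreed" before any analysis. That document is not shown.

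**The concern.** A 12-month Qmax can be absent for two quite different reasons. The man may have been lost to follow-up, so that his flow is unknown. Or he may have a catheter, so that his voiding status is known and poor. The article does not separate the two. As written, both fall under multiple imputation in the primary analysis, and both drop out of the complete-case analysis.

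The trial tests equivalence on Qmax with a margin of 4 ml/s. If one operation leaves more men catheter-dependent, that difference would not appear in any stated Qmax analysis. Men presenting in retention are eligible, form a randomisation stratum and are the subject of a secondary research question, so that subgroup comparison may be the most exposed.

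**Working it through.** **1. The plan's own figures.** Inputs from Sample size: margin 4 ml/s, assumed true difference 0.4 ml/s, SD 9 ml/s, 163 per arm, two-sided alpha 5%. With two one-sided tests, power = Φ((4 − 0.4)/se − 1.96) + Φ((4 + 0.4)/se − 1.96) − 1, where se = 9 × √(2/163) = 0.997. This gives Φ(1.65) + Φ(2.45) − 1 = 94.4%, against the stated 85%. The mismatch is a separate matter. It means the stated inputs do not make the trial too small, and it does not affect this point. I use 94.4% as the reference below.

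**2. What imputation can do with these men.** Under the collection rule, no man with a catheter at 12 months has an observed 12-month Qmax. Adding catheter or TWOC status as a predictor does not help, because the data hold no observed outcome from which to estimate its effect. An earlier low Qmax could pull an imputed value down, but the relation used would still be the one seen in men who void. Standard imputation therefore gives approximately the voiders-only comparison.

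**3. Size of the distortion.** Let fT and fC be the catheterised shares under ThuVARP and TURP, μ the TURP voiders' mean, and d the difference (ThuVARP minus TURP) among voiders.
- Voiders-only or imputed difference: d
- Difference with catheterised men scored zero: D = (1 − fT)(μ + d) − (1 − fC)μ
- Gap between them: d − D = fT(μ + d) − fC·μ, which is (fT − fC)·μ when d = 0

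The article gives neither μ nor the shares. Assumed range for μ: 15 to 25 ml/s. With d = 0:

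| ThuVARP / TURP catheterised | μ = 15 | μ = 20 | μ = 25 |
|---|---|---|---|
| 5% / 5% | 0 | 0 | 0 |
| 5% / 1% | 0.6 | 0.8 | 1.0 |
| 10% / 2% | 1.2 | 1.6 | 2.0 |

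Hiding the full 4 ml/s needs a gap of 4/μ, which is 27, 20 or 16 percentage points.

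**4. Effect on the decision.** Take μ = 20 and 163 men per arm with known voiding status. Equivalence is declared when the 95% interval lies within ±4. The probability follows the formula in step 1, with D or d in place of 0.4. For zero-scoring, se = √((vT + vC)/163), where each arm's variance is v = (1 − f)·81 + f(1 − f)·(voiders' mean)². For voiders only, se = 9 × √(1/(163(1 − fT)) + 1/(163(1 − fC))).

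| Shares, d | D | Voiders only | Zero-scored |
|---|---|---|---|
| 2% / 2%, d = 0 | 0 | 95.6% | 94.3% |
| 5% / 5%, d = 0 | 0 | 94.9% | 91.6% |
| 5% / 1%, d = 0 | −0.8 | 95.4% | 85.6% |
| 10% / 2%, d = 0 | −1.6 | 94.6% | 58.9% |
| 5% / 1%, d = +2 | +1.1 | 50.6% | 77.7% |

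A 4,000-run simulation of the same five cases agrees to about 2 percentage points; the largest gap is 83.6% against 85.6% for the zero-scored 5% / 1% case with d = 0. In the last row ThuVARP has more failures but better-flowing voiders, and leaving out the failures moves the result away from equivalence.

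**The case against.** The strongest reply is that the article does not describe the imputation model, does not say that a Qmax withheld because of a catheter counts as missing, and promises a full analysis plan. Coding of special cases usually sits there, and the baseline example shows that the team had thought about men who cannot void. This stands in part. The SAP could set a value for these men, and nothing in the article prevents it. It does not remove the point, because the rules that are stated, taken together, leave a known outcome state uncounted. As step 2 shows, a richer imputation model would not repair that; an explicit rule is needed.

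A reader might infer that these men will be analysed as normal voiders. The article does not say so. That is what standard imputation would approximately do.

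A reader might also infer a bias towards equivalence. That is not supported as a general statement. With equal shares and no difference among voiders the mean difference is unbiased, although zero-scoring still costs some precision. With unequal shares the direction depends on which arm has more failures and how its voiders compare.

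The baseline zero is an example for a covariate in a sensitivity analysis, so the plan is not breaking a coding rule of its own. Failures may also show in complications, catheterisation time, satisfaction and IPSS. Those outcomes inform interpretation but do not correct the Qmax comparison.

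**Conclusion.** The point holds in a limited form. Under the stated rules, no analysis of 12-month Qmax treats a man known to need a catheter as a failure, and complete-case analysis cannot reveal the consequence because it omits the same men. The possible distortion is about the rate gap times the voiders' mean. It is at most about 1 ml/s for a gap of 4 points, and is large enough to change the conclusion readily only when the gap nears 10 points. These sizes rest on an assumed voiders' mean of 15 to 25 ml/s and on assumed catheterisation shares. The article gives no 12-month rate and no reason to expect a gap between arms. For that reason this should be settled before the data are seen by arm, but it does not by itself invalidate the primary analysis.

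**What to change.** In the SAP, before any comparison by arm:
- Define catheter dependence at 12 months from the TWOC and visit data already recorded, and separate these men from men lost to follow-up.
- Restrict multiple imputation of Qmax to men whose 12-month voiding status is unknown.
- Give catheter-dependent men a failure value, for example Qmax = 0 in line with the baseline suggestion. Do this in the primary analysis or, at minimum, in a pre-specified sensitivity analysis shown beside the imputed result.
- Report the number and proportion catheter-dependent by arm next to the Qmax result.
- For IPSS, use the items that were answered, and test a poor value only as a sensitivity analysis. Imposing the worst score would give a few men great leverage on an outcome with an assumed SD of 5, and would override answers they can give.

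**Cost.** SAP wording and a little code, with no new data. The outcome gains a small spike at zero. Assuming μ = 20, SD = √((1 − p)·81 + p(1 − p)·400), which is 9.34 at p = 2% and 9.65 at p = 4%. With a true difference of 0.4 ml/s, Qmax power falls from 94.4% to 92.5% and 90.5%, still above the stated 85%.
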